### Sample size {14}

The clinical aim is to detect a mean difference in FEV_1_
*z*-scores of 0.3 at the age of 5 years [9]. Based on the values of the GNN study, the *z*-score standard deviation is expected to be 1.07. The significance level alpha is set to 0.05 (two-sided) and power to 0.8. To detect this effect using a two-sample *t*-test, it requires data from 201 patients per group. The total sample size is calculated on the following assumptions: adjustment for multiple births (10%), rate of patients dying before discharge (2%), loss to follow-up rate (28%), and the rate of patients who will not be able to accomplish lung function tests at the age of 5 years (10%). Based on these estimates, we calculated that data from 349 patients per group are needed (698 patients in total, nQuery 7.0).

### Recruitment {15}

At the time of this report, patients are recruited in 20 neonatal intensive care units in Germany. Names of site investigators and affiliations are given in the “Acknowledgements” section. Enrolment of one or two patients per month per centre will ensure enrolment of the target sample size within 30 months. However, the pro.LISA study group will recruit and initiate additional sites.

### Assignment of interventions: allocation

#### Sequence generation {16a}

A stratified permuted block randomisation is used with stratification by gestational age (25 and 26 weeks vs. 27 and 28 weeks), multiple birth status, and participating study centres. The randomisation lists are prepared by the Institute of Medical Biometry and Statistics.

#### Concealment mechanisms {16b}

Sequentially numbered opaque, sealed envelopes are provided to participating centres for the allocation of patients.

#### Implementation {16c}

Generation of allocation sequence and provision of randomisation envelopes is done by persons and institutions who are not involved in patient enrolment.

### Assignment of interventions: blinding

#### Who will be blinded {17a}

Blinding of physicians and nurses for the intervention is not possible in this study. Parents and outcome assessors of the primary outcome at age 5 years will be blinded to the procedure.

#### Procedure for unblinding if needed {17b}

Since physicians are not blinded, this will be not relevant.

### Data collection and management

#### Plans for assessment and collection of outcomes {18a}

Data of the pro.LISA trial are collected in an online database in the Castor EDC system [12]. Assessment forms for follow-up until 5 years of age are defined and implemented in the database. The time of regular assessments is given in the “Participant timeline {13}” section, and methods for outcome measures are given in the “Outcomes {12}” section.

#### Plans to promote participant retention and complete follow-up {18b}

We expect that follow-up until discharge from the hospital will be very close to 100%. For long-term follow-up, we are planning to contact parents every 6–12 months via phone or mail to minimise loss to follow-up.

#### Data management {19}

All study data are collected at a central online database. Details for data security and storage are given on the website [12]. To improve data quality at data entry, we established range checks for data values in the pro.LISA online database.

#### Confidentiality {27}

Since we need the contact information of parents for follow-up, these data are entered in the pro.LISA online database. Access to the pro.LISA online database is limited to investigators (who have only access to patient data of their own site) and qualified personnel from the study centre (University of Lübeck).

#### Plans for collection, laboratory evaluation, and storage of biological specimens for genetic or molecular analysis in this trial/future use {33}

In the pro.LISA trial, no biological specimens are collected. We encourage parents to participate in the GNN cohort study in addition to the pro.LISA trial. In the GNN cohort study, deoxyribonucleic acid samples of participating infants are collected.

## Statistical methods

### Statistical methods for primary and secondary outcomes {20a}

All details of statistical analyses will be specified in the statistical analysis plan, which will be finalised before the inclusion of the last patient. The primary and other efficacy endpoints will be analysed in the full analysis population. Patients who died before the 5-year follow-up and patients who were not able to complete the lung function test will be excluded from the full analysis set. The primary endpoint will be tested in a generalised estimating equation model assuming Gaussian error and exchangeable correlation matrix using a two-sided Wald test at a significance level alpha of 0.05.

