### Outcomes {12}

The primary endpoint of this study is FEV_1_ at the age of 5 years determined by spirometry and adjusted for age, sex, height, and ethnicity according to Global Lung Function Initiative standards (FEV_1_
*z*-scores) [10]. Analysis of the primary endpoint will be done by comparing the intervention and control groups of the full analysis set. Secondary efficacy endpoints at the age of 5 years are as follows:FVC *z*-score according to [10]FEV_1_/FVC *z*-score according to [10]Length in metres of running track in 3-min running test according to [11]Cerebral palsy defined as Gross Motor Function Classification System value > 1Score in Movement Assessment Battery for ChildrenIntelligence assessed by Wechsler Preschool and Primary Scale of Intelligence (WPPSI) IVObstructive bronchitis (treated with inhaled or other drugs) in the last 12 months

Spirometry measures (FEV_1_, FVC, and FEV_1_/FVC-scores) and the length of the running track will be aggregated as mean values. Movement Assessment Battery for Children and WPPSI-IV-scores will be aggregated as median scores. Cerebral palsy and obstructive bronchitis will be analysed as proportions. Safety endpoints will be assessed at discharge from the hospital and at the age of 5 years and include death and complications of premature birth. All adverse events and serious adverse events will be reported.

The following safety endpoints will be assessed at discharge from the hospital:DeathIntraventricular haemorrhage (IVH, each grade)IVH grade III or IVPeriventricular leukomalacia (PVL)Abdominal operation due to focal intestinal perforation (FIP)Abdominal operation due to necrotising enterocolitis (NEC)Laser surgery, cryocoagulation, or anti-VEGF treatment of retinopathy of prematurity (ROP)Operation due to a persistent ductus arteriosus (PDA)PneumothoraxBronchopulmonary dysplasia (BPD, need of O_2_ or breathing assistance with 36 weeks p.m.)Death or BPDDuration of mechanical ventilation (in days)Duration for need of O_2_ (in days)Duration of need of any breathing assistance (ventilation or CPAP) (in days)Mechanical ventilation during stay in hospitalMechanical ventilation during the first 72 h of lifeHerniotomyAbdominal operation due to other reasonsLung bleeding where transfusion or intubation is requiredBody weightBody lengthOne of the endpoints in 1–10.

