#### Analysis population

**Table Tabc:** 

	Randomisation	SA	ITT	FA	PP
Violation of major exclusion criteria	IV	IV	IV	IV	–
Violation of major exclusion criteria	CO	CO	CO	CO	–
Wrong treatment	IV	CO	IV	IV	–
Wrong treatment	CO	IV	CO	CO	–
Other major protocol deviation	IV	IV	IV	IV	–
Other major protocol deviation	CO	CO	CO	CO	–
No data for FU	IV	IV	IV	–	–
No data for FU	CO	CO	CO	–	–
None of above	IV	IV	IV	IV	IV
None of above	CO	CO	CO	CO	CO

*SA* Safety analysis set, *ITT* Intention-to-treat population, *FA* Full analysis set, *PP* Per-protocol population, *IV and CO* Randomised or analysed in the intervention and control group, respectively, “–” excluded from the analysis

Safety endpoints will be evaluated in the safety analysis (SA) set. The primary endpoint and other efficacy endpoints will be evaluated in the full analysis (FA) sets. Where possible, secondary endpoints will be analysed in the intention to treat (ITT) analysis population.

As a sensitivity analysis, all efficacy endpoints will additionally be evaluated in other analysis populations including a per protocol population.

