### Methods in analysis to handle protocol non-adherence and any statistical methods to handle missing data {20c}

The primary and secondary endpoints can only be examined if the patients are able to conduct the tests. Patients who are not able to conduct the tests and patients who died before the assessment will be excluded from the full analysis set.

Other scenarios for not conducting a follow-up are the following: unattainability of a patient, absence at the follow-up appointment, or the parents do not want to attend the follow-up examination. For these scenarios, missing values might not be related to the outcome and be comparable to the observed values in the intervention and control groups, and these scenarios assume that values are missing at random or missing completely at random. Thus, a multiple imputation for the endpoints will be done.

No other imputations of missing data will be performed, and all other analyses will be based on complete cases.

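### The protocol does not settle which analysis set governs the non-spirometry secondary endpoints, and one stated rule would make cerebral palsy, motor score and IQ conditional on completing spirometry

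*Protocol article*

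**What the plan says.** Outcomes {12} lists the secondary efficacy endpoints at 5 years. Two come from spirometry (FVC and FEV1/FVC z-scores). Five do not: the 3-minute running test, cerebral palsy by Gross Motor Function Classification System level, Movement ABC, WPPSI-IV, and treated obstructive bronchitis in the preceding year.

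Four places bear on the set in which they are analysed:

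- Statistical methods {20a}: "The primary and other efficacy endpoints will be analysed in the full analysis population". It then removes deaths before the 5-year visit and says that "patients who were not able to complete the lung function test will be excluded from the full analysis set".
- Analysis population, text: "The primary endpoint and other efficacy endpoints will be evaluated in the full analysis (FA) sets". The next sentence reads "Where possible, secondary endpoints will be analysed in the intention to treat (ITT) analysis population". The section closes by promising repeat analyses in the remaining sets, the per-protocol set among them, to test how sensitive the efficacy results are.
- Analysis population, table: the only row that takes a child out of the full analysis set is the one for missing follow-up data. No row covers a child who attends but cannot do spirometry.
- Missing data {20c}: "Patients who are not able to conduct the tests and patients who died before the assessment will be excluded from the full analysis set". This refers to tests in general, not to spirometry. Multiple imputation is described for non-attendance, not for inability.

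**The concern.** Under the literal {20a} rule, a child with a recorded motor classification and a valid IQ score is left out of both analyses for failing a breathing test. Forced spirometry needs motor control and the ability to follow instructions, and several of these endpoints measure just those abilities. If the children who cannot do it are more often impaired, the analysed rates are too low, absolute differences between arms shrink, and power falls. If the pattern of inability differs between arms, a difference can appear where none exists. Objectives {7} makes motor development and intelligence secondary hypotheses, so these comparisons are ones the trial intends to draw conclusions from.

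The conflict is a problem in itself. With two rules on the page and no order of precedence, the set for cerebral palsy or IQ could be chosen after the results are known.

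**Working it through.** **Reproducing the plan's figures.** Inputs from Sample size {14}: difference 0.3, SD 1.07, two-sided alpha 0.05, power 0.8; 10% for multiple births, 2% deaths before discharge, 28% lost to follow-up, 10% unable to do lung function tests.

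- Two-sample t-test: 200.66, so 201 per group, as stated.
- Inflation: 201 × 1.10 / (0.98 × 0.72 × 0.90) = 348.2, so 349 per group and 698 in total, as stated.

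The 10% unable is therefore already allowed for in the FEV1 sample size.

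**Children affected.**

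- Alive and followed up: 698 × 0.98 × 0.72 ≈ 493, about 246 per arm.
- Unable to do spirometry: 0.10 × 493 ≈ 49.
- Full analysis set under the literal {20a} rule: about 443, about 222 per arm.

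**Effect on cerebral palsy prevalence.** The protocol gives no cerebral palsy rate, no reasons for inability and no overlap between the two, so these are assumptions. Let p be the prevalence among children followed up and u the share of cases who cannot do spirometry. With 10% of all children excluded, the analysed prevalence is p(1 − u)/0.90, and the prevalence among the excluded is p·u/0.10. For p = 6%:

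| u | Analysed prevalence | Prevalence among the excluded |
|---|---|---|
| 10% (no association) | 6.0% | 6% |
| 30% | 4.7% | 18% |
| 50% | 3.3% | 30% |
| 80% | 1.3% | 48% |

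**Effect on an arm comparison.** Assume true rates of 10% and 5%, the same u in both arms, and no allowance for correlation between siblings:

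| Set | Rates | Difference | Power |
|---|---|---|---|
| All followed up | 10.0% v 5.0% | 5.0 points | about 56% |
| Full analysis set, u = 10% | 10.0% v 5.0% | 5.0 points | about 52% |
| Full analysis set, u = 50% | 5.6% v 2.8% | 2.8 points | about 31% |
| Full analysis set, u = 80% | 2.2% v 1.1% | 1.1 points | about 15% |

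The risk ratio is 2 in every row, because the factor (1 − u)/0.90 cancels. If u differs between arms, it does not cancel: with 6% in both arms and u of 30% in one and 50% in the other, the analysed rates are 4.67% and 3.33%, a spurious difference of about 1.3 points.

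**Effect on the medians.** Outcomes {12} says "Movement Assessment Battery for Children and WPPSI-IV-scores will be aggregated as median scores". Suppose all of the excluded 10% could have been scored and all lay below the median. The analysed median would then sit at 0.10 + 0.5 × 0.90 = 0.55 of the full distribution, the 55th percentile instead of the 50th. That is the upper bound of the upward shift within an arm.

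**The case against.** The strongest reply is that the plan can be read sensibly as it stands. The sentence on the intention-to-treat population is the more specific rule for secondary endpoints, and cerebral palsy and obstructive bronchitis can be recorded without spirometry, so that population is feasible for them. Section {20c} speaks of the tests in the plural and can be taken test by test. The table has no exclusion for failed spirometry. Sensitivity analyses in other populations would probably bring the dropped children back in. The full analysis plan, which is not shown, may settle the matter.

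Much of this stands. A reader might infer that the plan has settled on removing impaired children from the endpoints that measure impairment. The documents do not support that: full analysis set and intention-to-treat rules stand side by side, and the link between failed spirometry and impairment is an inference, with no association as one possible case. A reader might also infer a failure of safety reporting. The safety endpoints use the safety set, which carries no spirometry condition and includes intraventricular haemorrhage, periventricular leukomalacia and general development at 5 years. Nor is every effect measure diluted: if equal shares of cases are excluded in both arms, the risk ratio is unchanged.

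What the reply does not remove is the conflict. The full analysis set rule is stated twice for efficacy endpoints other than the primary. The feasibility proviso on intention to treat is undefined. Section {20c} still removes the whole child from the set. A sensitivity analysis does not say which result is the main one. This is a stated rule that contradicts another, not detail left to a later document.

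**Conclusion.** The concern holds as an unresolved conflict between {20a}, the analysis population section with its table, and {20c}. One of the available readings conditions five non-spirometry secondary endpoints on completing spirometry. On the plan's own rates, that reading drops about 49 of about 493 children. The loss of about 10% of the observed sample follows from the protocol, assuming the 10% applies to children who attend. Any bias in rates rests on the assumed prevalence and overlap, and ranges from none to substantial: 6.0% down to 1.3% in the illustration. FEV1, the primary test and the sample size are untouched. This should be fixed; it does not threaten the trial's main result.

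**What to change.** - Define the analysis set for each endpoint. For spirometry endpoints: children with a valid spirometry. For each of the other secondary endpoints: all randomised children with that assessment, analysed as randomised, whatever their spirometry result.
- State that inability to do spirometry excludes a child from the spirometry endpoints only.
- Remove the feasibility proviso on intention to treat, or define it, and name the one set that governs each secondary endpoint.
- Align {20a}, the text and table on analysis populations, and {20c}, and carry the same definitions into the statistical analysis plan.

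The cost is wording: no new data and no change to the sample size. It should be done before any 5-year data are seen by arm. Assigning a floor score to children too impaired for Movement ABC or WPPSI-IV is one option the sponsor may consider separately; the fix does not depend on it.

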#### Analysis population

**Table Tabc:** 

	Randomisation	SA	ITT	FA	PP
Violation of major exclusion criteria	IV	IV	IV	IV	–
Violation of major exclusion criteria	CO	CO	CO	CO	–
Wrong treatment	IV	CO	IV	IV	–
Wrong treatment	CO	IV	CO	CO	–
Other major protocol deviation	IV	IV	IV	IV	–
Other major protocol deviation	CO	CO	CO	CO	–
No data for FU	IV	IV	IV	–	–
No data for FU	CO	CO	CO	–	–
None of above	IV	IV	IV	IV	IV
None of above	CO	CO	CO	CO	CO

*SA* Safety analysis set, *ITT* Intention-to-treat population, *FA* Full analysis set, *PP* Per-protocol population, *IV and CO* Randomised or analysed in the intervention and control group, respectively, “–” excluded from the analysis

Safety endpoints will be evaluated in the safety analysis (SA) set. The primary endpoint and other efficacy endpoints will be evaluated in the full analysis (FA) sets. Where possible, secondary endpoints will be analysed in the intention to treat (ITT) analysis population.

As a sensitivity analysis, all efficacy endpoints will additionally be evaluated in other analysis populations including a per protocol population.

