## Introduction

### Background and rationale {6a}

Less invasive surfactant administration (LISA) describes intratracheal surfactant administration via a small diameter tube to spontaneously breathing infants [1]. The current guidelines recommend surfactant therapy in preterm infants if the fraction of inspired oxygen (FiO_2_) is higher than 0.30 and LISA as the optimal mode of administration for preterm infants on continuous positive airway pressure (CPAP) [2]. This recommendation is based on a number of randomised controlled trials and meta-analyses [3–7]. The use of prophylactic LISA in infants with FiO_2_ at or below 0.30 was not yet tested in randomised controlled trials.

Observational data from the GNN indicate that in infants with gestational age 25–28 weeks and FiO_2_ ≤ 0.30, LISA treatment rates are as high as 50%. Reasons for this high rate of LISA despite the lack of data and high costs of surfactant therapy are unclear.

Prophylactic surfactant therapy via an endotracheal tube is not superior to early CPAP and selective surfactant treatment of infants requiring intubation [8]. Furthermore, even LISA causes some stress for preterm infants, since the trachea is intubated with a small diameter tube, which can induce discomfort, coughing, desaturations, tracheal obstruction, and bradycardia. Possible benefits of LISA prophylaxis include a lower rate of intubation and mechanical ventilation and better long-term lung function [9]. The existing uncertainties concerning LISA prophylaxis prompted us to design and initiate the pro.LISA trial.

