The following safety endpoints will be assessed at the age of 5 years:General healthDevelopment compared to children of the same ageSystolic blood pressure (1st measurement)Systolic blood pressure (2nd measurement)Medium blood pressure (1st measurement)Medium blood pressure (2nd measurement)Diastolic blood pressure (1st measurement)Diastolic blood pressure (2nd measurement)Heart rateBreathing rateSpO_2_Systolic blood pressure after running testDiastolic blood pressure after running testMedium arterial pressure (MAD) after running testHeart rate after running testBreathing rate after running testSpO_2_ after running test

Safety endpoints will be compared in the safety analysis dataset. The method of aggregation for safety endpoints until discharge will be proportions for numbers 1–11, 15–19, and 22 and median values for 12–14 and 20–21. The method for aggregation of data at 5-year follow-up will be proportions for items 1–2 and mean values for all other endpoints. All statistical analyses are described in detail in the statistical analysis plan, which will be finalised before the randomisation of the last patient in the study.

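### Death, BPD and ventilation are assigned only to an as-treated safety set, so the early report on short-term benefit is not fully as randomised if infants cross over

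*Protocol article*

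**What the plan says.** In the protocol article, Outcomes {12} lists the endpoints assessed at discharge under the safety heading. They include death, BPD, death or BPD, duration of mechanical ventilation, and ventilation in the first 72 h and during the hospital stay.

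The analysis set is fixed in two places. Outcomes {12} says "Safety endpoints will be compared in the safety analysis dataset", and the section Analysis population says "Safety endpoints will be evaluated in the safety analysis (SA) set".

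The table in Analysis population defines that set. In the two rows headed "Wrong treatment", an infant randomised to intervention is counted as control in the safety set, and an infant randomised to control is counted as intervention. The ITT and full analysis sets keep the randomised arm.

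As-randomised analysis is offered elsewhere: "Where possible, secondary endpoints will be analysed in the intention to treat (ITT) analysis population". The list of those endpoints opens with "Secondary efficacy endpoints at the age of 5 years are as follows" and contains none of the discharge outcomes. The sensitivity analyses have the same limit: "As a sensitivity analysis, all efficacy endpoints will additionally be evaluated in other analysis populations including a per protocol population".

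The rationale {6a} nevertheless states: "Possible benefits of LISA prophylaxis include a lower rate of intubation and mechanical ventilation and better long-term lung function". Dissemination plans {31a} foresees a descriptive report of discharge outcomes before the 5-year result. The Discussion says the trial will inform whether short-term benefits outweigh the stress, discomfort and cost of the procedure.

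**The concern.** An as-treated set is a usual choice for harms of a procedure. Here the safety list also carries the short-term efficacy question, and the article states no as-randomised comparison for it.

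An as-treated comparison keeps the protection of randomisation only if departures from allocation are unrelated to prognosis. Several features of the design make a relation possible:

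- Treating staff are not blinded (section {17a}).
- No adherence strategy is defined (section {11c}).
- The Abstract reports that about half of such infants already receive LISA in practice.
- Controls may receive LISA if the physician sees respiratory distress (Control group), and the article gives no rule that separates this from the prophylactic surfactant prohibited in section {11d}.

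An infant's condition in the first hour could therefore influence both the treatment received and later ventilation, BPD or death. At stake is the first published comparison of the arms, years before the primary result. The primary endpoint is not affected, because the full analysis set keeps the randomised arm.

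**Working it through.** **The plan's own figure.** The article gives no figure for the safety comparison. The only design figure needed is the number randomised, and it reproduces: 201 × 1.10 / (0.98 × 0.72 × 0.90) = 221.1 / 0.635 = 348.2, hence 349 per group.

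**Inputs.** From the article: n = 349 per arm, 2% deaths before discharge (Sample size {14}), and expected prophylactic LISA of 100% against 0% (Discussion). Assumed: an event rate p = 25% for an outcome such as BPD or ventilation; a share c of the intervention arm that misses LISA and is counted as control; and a risk in those infants r times the arm average. There is no true treatment effect.

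**Expected rates in the safety set.**

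- Intervention: p(1 − cr)/(1 − c)
- Control: p(1 + cr)/(1 + c)

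Example with c = 5% and r = 2: 0.25 × 0.90/0.95 = 23.7%, and 0.25 × 1.10/1.05 = 26.2%.

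To put the bias on a familiar scale, I also give the probability that a nominal two-sided 5% test of two proportions rejects. With δ the difference, SE0 the pooled and SE1 the unpooled standard error, it is Φ((−1.96·SE0 − δ)/SE1) + Φ((−1.96·SE0 + δ)/SE1). For c = 5%, δ = −0.0251, SE0 = 0.0328 and SE1 = 0.0328, which gives 11.8%.

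| Crossover c (p = 25%, r = 2) | Intervention | Control | Difference, points | Rejection rate |
|---|---|---|---|---|
| 0% | 25.0% | 25.0% | 0 | 5.0% |
| 2% | 24.5% | 25.5% | −1.0 | 6.1% |
| 5% | 23.7% | 26.2% | −2.5 | 11.8% |
| 10% | 22.2% | 27.3% | −5.1 | 33% |

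Analysed as randomised, the expected difference is 0 and the rejection rate 5% in every row. If r = 1, the safety set is unbiased too.

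**Direction.** If instead 5% of controls, at double risk, receive LISA and are counted as intervention, the formulas swap and the difference is +2.5 points, against LISA. If 5% of each arm cross over at double risk, the two cancel.

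**Mortality at the stated 2%.**

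- c = 2%: −0.08 points (r = 2) and −0.16 points (r = 3).
- c = 5%: −0.20 points (r = 2) and −0.40 points (r = 3; 1.79% against 2.19%).
- c = 10%, r = 3: −0.8 points.

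**The case against.** The strongest defence is that crossover may be negligible. Infants must be breathing spontaneously with adequate saturation at low oxygen to be enrolled, the treatment follows at once, and it takes 1 to 3 minutes. With the expected 100% against 0%, the safety and ITT sets coincide and nothing is biased. The commonest apparent crossover, rescue LISA in about half of the controls, is permitted care and not by itself wrong treatment. The early report is described as descriptive, with no test or alpha stated. As-received safety sets are conventional, and the statistical analysis plan, not shown, may add an as-randomised table.

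Most of this stands as a limit on size. It does not remove the point. The expected adherence is an expectation with no strategy behind it. A descriptive estimate carries the same bias as a tested one. The article fixes the safety set for these outcomes in two places, so this is a stated choice and not a detail left open.

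A reader might go further and infer that the rule will manufacture a short-term benefit, for example because infants intubated before LISA are moved to control together with their ventilation event. If 20% of each arm (70 of 349) were ventilated and 17 intervention infants, all ventilated, were moved, the safety set would show 53/332 = 16.0% against 87/366 = 23.8%, p = 0.01. The article does not support that reading:

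- It does not say that such an infant counts as wrong treatment. The table has a separate row for other major deviations, which keeps the randomised arm.
- Neither the 5% crossover nor the 20% event rate comes from the article.
- Having every moved infant ventilated makes crossover and outcome the same event. If 60% of them are ventilated, the result is 17.9% against 21.9%, with p about 0.19.
- The bias can equally run against LISA.

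**Conclusion.** The point holds as a should-fix. As written, death, BPD, death or BPD, and ventilation are compared only in an as-treated set, although some of these outcomes are where the article looks for benefit. The early report would then not be a fully as-randomised comparison if treatment received depends on the infant's early condition.

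The bias is nil at the expected adherence and minor at 2% crossover. For common outcomes it becomes material at around 5% to 10% crossover by infants at clearly higher risk. For mortality it stays within a few tenths of a point at 2% to 5% crossover. These sizes rest on assumed crossover shares, relative risks and a 25% event rate; only the 349 per arm and the 2% death rate come from the article. A benefit in a fixed direction cannot be predicted.

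**What to change.** In Outcomes {12} and Analysis population, and correspondingly in the statistical analysis plan before it is finalised:

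- Make the ITT set, as randomised, the main set for death, BPD, death or BPD, mechanical ventilation and the other discharge outcomes used to judge short-term benefit, including in the short-term publication.
- Keep the as-treated safety set as a supportive analysis, mainly for procedure-related events.
- Define wrong treatment, so that rescue LISA permitted in the control group is not counted as crossover and it is clear which departures move an infant to the other arm.

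The ITT set is already defined. The cost is a few sentences and one additional set of tables, with no change in sample size. If adherence is perfect, the two analyses agree and nothing is lost.
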